#### Inclusion criteria

Participants in the 10th to 12th grade (mean ages 15–16 at baseline for the intervention group and 17–18 years for the control group) will be enrolled. Informed consent by the participant and, for participants younger than 18 years, their legal representative will be obtained. Consent for inclusion of data from the “mother-child booklet” additional maternal informed consent will be obtained.

Schools and training companies will be randomly assigned to either the intervention or the control group. The examination of the intervention group will start first. Schools will be assigned to either group according to their available schedule. The exact number of participating schools/training companies will depend on the number of participants per school/company.

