# The Tyrolean early vascular ageing-study (EVA-Tyrol): study protocol for a non-randomized controlled trial

**DOI:** 10.1186/s12872-020-01357-9

**Published:** 2020-02-05

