**Methods:**

The EVA-Tyrol study is a population-based non-randomized controlled trial that will prospectively enroll 2000 participants from high schools and training companies in North- and East-Tyrol (Austria) and South-Tyrol (Italy). Participants will be assigned to either an intervention (*n* = 1500) or a control (*n* = 500) group. Intervention group participants will be enrolled at the 10th school grade (mean age 15–16 years), undergo two examinations within a two-year interval, with follow-up at the 12th grade (mean ages 17–18 years). Control group participants will be enrolled at the 12th grade (mean age 17–18 years). Medical examination will include anthropometric measurements, comprehensive lifestyle and dietary questionnaires, a fasting blood sample, high-resolution ultrasound of the carotid arteries, and measurement of carotid-femoral pulse wave velocity. Active intervention will consist of (1) enhancing knowledge about CVDs, (2) individual medical counseling based on the results of the baseline examination, (3) an online health promotion tool and (4) involvement of participants in planning and implementation of health promotion projects. Effectiveness of the intervention will be assessed by comparing the proportion subjects with ideal health metrics as defined by the American Heart Association between study groups.

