## Methods and design

### Study design

The EVA-study is a non-randomized controlled trial. Two thousand participants will be recruited from high schools and training companies spread over North- and East-Tyrol (Austria) and South-Tyrol (Italy). Study participants will be assigned to i) health intervention group (*n* = 1500) or ii) control group (*n* = 500). For participants included in the intervention group two examinations will be scheduled within a two-year interval between the examinations. Participants will be in the 10th grade (mean age, 15–16 years) at the baseline and in the 12th grade (mean age, 17–18 years) at the follow-up examination. Between the examinations the health intervention program will be offered.

Five hundred participants with a mean age of 17–18 years without participation in a health promotion program will serve as a control group. The prevalence of AHA health metrics in the intervention group will be compared to the prevalence in the control group (Fig. 1).

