### Outcome measures and statistical analysis

The *primary outcome measure* will be the difference in the proportion of each of AHA’s seven health metrics in the ideal range between the intervention and the control group.

The *secondary outcome measure* will be the change in the proportion of AHA’s seven health metrics in the ideal range between baseline and follow-up in the intervention group.

*Further descriptive and exploratory analysis* will focus on the prevalence of unfavorable health behaviors, the prevalence of vascular risk conditions and the change of these factors over age as well as their influence on EVA measured by IMT and the PWV. In addition, the influence of premature birth and early life weight gain (taken from the mother-child-booklet) on obesity and other components of the metabolic syndrome in youth will be explored.

Differences in proportions of the individual health metrics in the ideal range between the intervention and control group (primary outcome parameter) will be analyzed by Chi-squared test. The Prevalence of the individual health metrics in the ideal range in a similar cohort [18] varied from < 5% for ideal diet, over around 50% for ideal physical activity to > 80% for ideal body-mass index. On the basis of a 3:1 intervention to control group split, power analysis indicates that 95% power can be achieved with a sample size of 2000 to detect differences in proportions between intervention and control group of 3% (at a control group proportion of 96%) to 10% (at a control group proportion of 50%) [33] .Multivariate analysis will be done by logistic regression.

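### Allocation of schools is stated both as random and as by availability in a trial labelled non-randomised; the random statement is unsupported, and the unadjusted primary test cannot carry a causal conclusion

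*Protocol article*

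**What the plan says.** The protocol article describes how groups are formed in four places.

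- Title: "study protocol for a non-randomized controlled trial".
- Abstract, Methods: "The EVA-Tyrol study is a population-based non-randomized controlled trial".
- Study design: "The EVA-study is a non-randomized controlled trial".
- Inclusion criteria, second paragraph, in three consecutive sentences. The opening one claims chance allocation: "Schools and training companies will be randomly assigned to either the intervention or the control group". The middle one concerns timing only: "The examination of the intervention group will start first". The third then gives a different rule for forming the groups: "Schools will be assigned to either group according to their available schedule".

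Under Outcome measures and statistical analysis, the primary outcome is the between-group difference in the share of participants in the ideal category on each of the seven AHA metrics. It is tested by chi-squared. The same section plans a multivariate logistic regression but does not make it the primary analysis. The sample size statement there starts "On the basis of a 3:1 intervention to control group split" and says that "95% power can be achieved with a sample size of 2000".

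**The concern.** The allocation mechanism decides how a difference between the groups may be read. If chance decides which schools receive the programme, a difference beyond sampling error can be attributed to the programme. If a school's own circumstances decide, the difference mixes the programme's effect with whatever else separates the two sets of schools. The Inclusion criteria paragraph gives both mechanisms, and the rest of the article supports only the second.

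The conclusion the trial can draw is at stake. The abstract presents the study as a demonstration that the programme works, and the primary test makes no adjustment for differences between schools. Someone assessing risk of bias will go to the allocation paragraph, and the first statement there is the random one.

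**Working it through.** **1. Can the statements all be true?**

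- *Random against schedule.* Both sentences concern the same decision, namely which group a school joins. The second does not say that the schedule fixes only the examination date; it says that the schedule fixes the group. If availability determines the group, chance does not. The two are incompatible for schools. The schedule sentence names only schools, so training companies could in principle be handled differently, but the random sentence covers schools as well and the conflict remains.
- *Random against the design label.* Title, abstract and Study design all say non-randomised. Random assignment of schools would make this a cluster-randomised trial.
- *Schedule against the design label.* These agree.
- *Is there a reconciling rule?* The article gives no random sequence, and no step in which chance operates before or after the schedule.

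Three design labels and the schedule rule fit together. The random-assignment sentence stands alone.

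**2. The plan's own figure.** Inputs from Outcome measures and statistical analysis: 500 controls, 1500 intervention participants, 3 points at a control proportion of 96%, 10 points at 50%. Alpha is not stated; two-sided 0.05 is assumed.

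Formula: power = Φ[(d − 1.96·SE₀)/SE₁]. SE₀ uses the pooled proportion and SE₁ the separate proportions. Note that 1/500 + 1/1500 = 0.002667.

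- 96% against 99%: pooled proportion (480 + 1485)/2000 = 0.9825; SE₀ = √(0.9825 × 0.0175 × 0.002667) = 0.00677; SE₁ = √(0.96 × 0.04/500 + 0.99 × 0.01/1500) = 0.00913; power = Φ[(0.03 − 0.01327)/0.00913] = Φ(1.83) = 96.7%.
- 50% against 60%: pooled proportion (250 + 900)/2000 = 0.575; SE₀ = 0.02553; SE₁ = 0.02569; power = Φ[(0.10 − 0.05003)/0.02569] = Φ(1.945) = 97.4%.

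Both fit the stated 95% with the differences rounded up. The contradiction over allocation changes neither figure.

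**3. What the primary test relies on.** For any one metric, write the expected difference between groups as

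E(p_I − p_C) = δ + b,

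where δ is the programme's effect and b is the difference that the two groups would have shown without the programme. Under random assignment of schools, b averages zero over possible allocations. Under assignment by availability, nothing sets b to zero. The chi-squared test addresses δ + b = 0. It answers the question about δ only if b = 0, which the random-assignment sentence would justify and the schedule rule does not. The document gives no figure from which b could be estimated.

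**The case against.** The strongest reply is that the trial declares itself non-randomised in the title, abstract and design section. On this view the random-assignment sentence is one loose phrase, perhaps meaning no more than haphazard. Much of this stands. A reader might infer that the plan as a whole claims to be cluster-randomised, but the document does not support that: one sentence says so against three labels. The sentence is still wrong as written, and it stands where allocation is defined.

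The reply also notes that logistic regression is planned. That is true, and the choice of covariates may properly be left to a document not shown. However, the article names the chi-squared test for the primary outcome and gives the regression no primary role.

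Three stronger readings are tempting and are not supported:

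- *Early schools are the motivated ones, so the programme will look better than it is.* Nothing links availability to motivation. The Recruitment section says that schools apply and that principals of selected schools are encouraged to join, to balance region and social mix. It draws no distinction between the groups.
- *Group is confounded with calendar time because intervention examinations start first.* Intervention participants are examined again two years later, in 12th grade, while controls are examined once, in 12th grade. An early start for the intervention group could bring the control visits closer in time to that follow-up. The figures showing the timeline are not available, so this cannot be settled.
- *The false-positive rate is 21% to 49%.* At 50% prevalence SE = √(0.25 × 0.002667) = 2.58 points. A pure bias of 3, 4 or 5 points then gives z = 1.16, 1.55 or 1.94, and a significant result in 21%, 34% or 49% of studies. The arithmetic is right, but the 3 to 5 points are assumed. The same result would hold for any non-randomised trial with that bias, so it does not measure the fault in this paragraph.

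**Conclusion.** The point holds as an internal contradiction with a consequence for interpretation. Assignment by a school's availability is not random, so the random-assignment sentence states a property that the design does not have. Without that property, the unadjusted chi-squared comparison describes a difference between groups but does not by itself support attributing the difference to the programme.

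The effect on the planned numbers is nil: sample size and stated power stand, assuming a two-sided 5% level and independent participants. The size and direction of any selection bias cannot be derived from the document, and no claim is made about either. The verdict assumes that the schedule sentence means what it says. If a random step did take place and was left out, the contradiction is one of reporting and the remedy is to describe that step.

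**What to change.** Keep one allocation rule.

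- **If the schedule decides:** delete the random-assignment sentence and state that allocation is non-random, by availability. Record the allocation date and reason for each school and company, and avoid randomised-trial wording in all reports. Base the between-group conclusion on the logistic regression already planned, adjusted for measured factors such as school or company type, region, sex and age. Keep the chi-squared test as the unadjusted description.
- **If a random step existed:** describe it, and say how it relates to the schedule rule.

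Two further measures are not recommended on this evidence. Adjusting for application date could leave little overlap between groups if date nearly determines group. Randomising remaining schools would mix two allocation mechanisms, and registration was retrospective in April 2019, so it is unknown whether any schools remained.

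The cost is one corrected paragraph, a short allocation log and slightly more analysis work. The causal claim also becomes more cautious, since adjustment for measured factors does not replace randomisation.

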#### Exclusion criteria

None; previous or concurrent diseases are not an exclusion criterion.

### Data acquisition

The study will take place at the schools’ or training companies’ sites. An overview of the trial procedures is depicted in Fig. 2. Data will be collected by a paper case report form (CRF) and include a self-administered and assisted questionnaire, a structured interview and a series of examinations (blood sampling, high-resolution ultrasound of the carotid arteries, tonometric measurement of carotid-femoral pulse-wave velocity, blood-pressure measurement and anthropometry). Data acquisition will be done by medical doctors assisted by medical students.

**Fig. 2 Fig2:**
[figure not shown]
SPIRIT diagram: Timeframe of EVA-Tyrol

#### Questionnaire

Table 1 shows the structure of the employed CRF. The CRF is adapted from the Bruneck- [27], ARMY- [16], ARFY- [17] and HBSC (Health Behavior in School Children Study)- [22] studies and organized in three parts: the first part of the CRF is self-administered, the second part has to be completed under group supervision of an MD. The third part is a structured face-to-face questionnaire by an MD about the study’s main outcome parameters and previous medical history of each participant (Table 1). The family history for diabetes, hypertension or CVDs, is explored separately for each condition and rated as present when at least one first or 2 s degree relatives became diseased at an early age (women < 65 years, men < 55 years).

**Table 1 Tab1:** Overview over the EVA-Tyrol questionnaire

Self-administered		
Overall health and life satisfaction, lifestyle factors, social background	21 items	Health Behaviour in School Children -Study [22]
Food habits	23 items	The Adolescent Food Habits Checklist [23]
Nutritional knowledge	16 items	Turconi score Section E, G and H [24]
Participation and perception of health promotion	12 items	
Assisted		
Baecke score for physical activity	20 items	[25]
Score for Allergic Rhinitis	9 items	[26]
Traffic-Exposure	3 items	Taken from the ARMY [16] and ARFY [17] studies
Food frequency questionnaire	90 items	Taken from the ARMY [16], ARFY [17] and Bruneck [27] studies
Face-to-face interview		
Dietary interview	7 items	According to the AHA health metrics for youth [11, 28]
Physical activity	1 item	Moderate- and vigorous-intensity activity (minutes per day), AHA health metrics for youth [11, 28]
Smoking and alcohol consumption	12 items	Adapted from the Bruneck Study [27, 29]
Classical cardiovascular risk-factors and previous diseases as well as chronic infections.	17 items	Structured interview for known hypercholesterolemia, diabetes, hypertonia, diseases of the heart, vasculature, thyroid glands, liver, lung, known neoplasias, chronic infections of lung, sinuses, urinary tract, skin or chronic dental infections.
Family history for CVD	3 items	Premature CVDs (women < 65 years, men < 55 years), hypertension or diabetes in one 1st or two 2nd degree relatives.
Allergies and atopic predisposition	11 items	Structured interview for history of allergies, clinical symptoms and medical therapy.
Headache history	8 items	Classification of the international headache society (ICHD-3) [30]
Medication use	9 items	Structured interview for previous and current medication use

Table 1 shows an overview of the three parts (self-administered, assisted and face-to-face) of the EVA-Tyrol questionnaire. Left column – topic, middle column – number of questions, right column – source/description of questionnaire

#### Mother-child booklet data

In 1974 the Austrian government introduced a mother-child booklet (“Mutter-Kind Pass”) aiming to improve the health of pregnant women and children [31]. It consists of predefined examinations of the mother, the fetus, and the newborn and extends until the age of 6 years. Results of these examinations are documented in a booklet. As the child’s continuous financial governmental support is dependent on the completion of all examinations, adherence to the suggested medical examinations is high. Data extracted from the mother-child booklet is shown in Table 2. The Italian mother-child booklet is similar in content except for minor differences in examination intervals.

**Table 2 Tab2:** Data extracted from the mother-child-booklet

Mother-child-booklet	
Maternal characteristics	Age at pregnancy Singleton/multiple pregnancy Body weight and length (begin and end of pregnancy) Blood pressure (begin and end of pregnancy) Smoking status (begin and end of pregnancy) Pre-existing conditions (diabetes, hypertension)
Pregnancy complications (yes/no)	Pathological oral glucose tolerance test Preeclampsia Hypertension Proteinuria
Characteristics of neonate	Date of birth Gestational age Apgar Score Umbilical blood pH Mode of birth Body weight Body length Head circumference
Data of the child of 8 follow-up examinations at week 4–7, month 3–5, 7–9, 10–14, 22–26, 34–38, 46–50 and 58–62	Date of examination Body weight Body length Head circumference

Table 2 shows an overview of the information extracted from the mother-child-booklet

#### Physical examination

Physical examination will be performed by study personnel. Anthropometric measurements will include size and weight as well as waist- and hip-circumference. Blood pressure will be measured three times in the sitting position after 5 min of rest by a standard digital haemodynamometer (Omron; Omron Healthcare, Lake Forest, Illinois, US) on both arms. High-resolution ultrasound of the carotid arteries will be performed with a portable GE medical Vivid_i_ ultrasound with a linear transducer 12 L RS probe (both General Electric, GE-Healthcare, Chicago, US). The intima-media thickness (IMT) will be assessed by experienced sonographers from the anterior and posterolateral view. Representative images will be stored digitally and IMT will be measured offline on the stored images on three representative locations in the distal proportion of the common carotid artery of both sides. Carotid-femoral pulse wave velocity and central blood pressure will be calculated as a surrogate for aortic stiffness from simultaneous recording of ten consecutive pulse waves of artefact-free cardiac cycles by applanation tonometry according to the manufacturer’s instructions (Complior-Analyze®, ALAMmedical, Paris, France).

#### Sample collection and analysis

Blood samples will be drawn after an overnight fastand will immediately be stored in cooling boxes at approximately 4 °C before direct transfer to the ISO-certified Central Institute for Medical and Chemical Laboratory Diagnostics of Innsbruck University Hospital. Parameters and measurement methods are detailed in Table 3. Long-term storage of serum and plasma samples will be at − 80 °C. The serum biobank will consist of serum and lithium-heparin plasma, as well as full blood for DNA extraction only for subjects that signed an additional informed consent form.

**Table 3 Tab3:** ‘Routine lab parameters and methodology'. HPLC High pressure liquid chromatography, ECLIA Electrochemiluminescenceimmunoassay

Parameter	Unit	Method	Reagent	Analyzer
Glucose	mg/dl	Hexokinase method	Roche	Cobas 8000
HbA1c (DCCT/NGSP)	%	HPLC	Menarini	HA 8180 T
HbA1c (IFCC)	mmol/mol	HPLC	Menarini	HA 8180 T
Insulin	mU/l	ECLIA	Roche	Cobas 8000
Cholesterol	mg/dl	Enzymatic color assay	Roche	Cobas 8000
HDL-Cholesterol	mg/dl	Enzymatic color assay	Roche	Cobas 8000
LDL-Cholesterol	mg/dl	Enzymatic color assay	Roche	Cobas 8000
Triglyceride	mg/dl	Enzymatic color assay	Roche	Cobas 8000
Lipoprotein (a)	nmol/l	Particle-enhanced immunological clouding assay	Roche	Cobas 8000
Total-Homocystein	umol/l	Chemiluminescence microparticle immunoassay	Abbott	Architect
Urea	mg/dl	Kinetic test with urease and Glutamate dehydrogenase	Roche	Cobas 8000
Creatinine (enzym.-IDMS)	mg/dl	Enzymatic color assay	Roche	Cobas 8000
Total-protein	g/dl	Biuret test	Roche	Cobas 8000
Uric acid	mg/dl	Enzymatic color assay with uricase	Roche	Cobas 8000
Potassium	mmol/l	Indirect potentiometry	Roche	Cobas 8000
Calcium	mmol/l	Photometric with 5-Nitro-5′-methyl-BAPTA	Roche	Cobas 8000
GOT (ASAT)	U/l	According to IFCC recommendations, though optimized	Roche	Cobas 8000
GPT (ALAT)	U/l	According to IFCC recommendations, though optimized	Roche	Cobas 8000
Gamma-GT	U/l	Enzymatic color assay	Roche	Cobas 8000
Creatine kinase	U/l	Enzymatic UV-Assay	Roche	Cobas 8000
C-reactive protein	mg/dl	Particle-enhanced immunological clouding assay	Roche	Cobas 8000
Ferritin	ug/l	Particle-enhanced immunological clouding assay	Roche	Cobas 8000
TSH	mU/l	ECLIA	Roche	Cobas 8000
Free thyroxine (FT4)	pmol/l	ECLIA	Roche	Cobas 8000
Thyroglobulin	ug/l	ECLIA	Roche	Cobas 8000
Thyroglobulin-Antibodies	kU/l	ECLIA	Roche	Cobas 8000
ESR after 1 h	mm/h	Westergren-Method	Mechatronics	Starrsed Auto Compact
Leukocytes	G/l	Biofluorescence/flow cytometry	Sysmex	XE-5000
Absolute number of Neutrophiles	G/l	Biofluorescence/flow cytometry	Sysmex	XE-5000
Erythrocytes	T/l	Impedance method	Sysmex	XE-5000
Haemoglobin	g/l	Photocolorimetric	Sysmex	XE-5000
Hematocrit	l/l	Impedance method	Sysmex	XE-5000
Platelets	G/l	Impedance method	Sysmex	XE-5000
MCH	pg	Calculated	Sysmex	XE-5000
MCHC	g/l	Calculated	Sysmex	XE-5000
MCV	fl	Calculated	Sysmex	XE-5000
Erythrocyte-distributional width	%	Calculated	Sysmex	XE-5000
Band neutrophiles	%	Manual microscopy	manual	Light microscopy
Segmented neutrophiles	%	Biofluorescence/flow cytometry and light microscopy	Sysmex	XE-5000
Lymphocytes	%	Biofluorescence/flow cytometry and light microscopy	Sysmex	XE-5000
Lymphocytes	G/l	Biofluorescence/flow cytometry and light microscopy	Sysmex	XE-5000
Monocytes	%	Biofluorescence/flow cytometry and light microscopy	Sysmex	XE-5000
Eosinophils	%	Biofluorescence/flow cytometry and light microscopy	Sysmex	XE-5000
Basophils	%	Biofluorescence/flow cytometry and light microscopy	Sysmex	XE-5000
Plasma cells	%	Manual microscopy	Manual	Light microscopy
Folic acid	μg/l	Competitive binding assay	Roche	Cobas 8000
Vitamin B12	pmol/l	ECLIA	Roche	Cobas 8000

